## Abstract

**Introduction:**

Musculoskeletal disorders are a major cause of disability worldwide, significantly impacting office workers due to prolonged sitting and lack of movement. Implementing therapeutic exercise interventions in the workplace has been identified as a feasible and cost-effective strategy to address spinal pain. However, understanding workers’ perspectives and workplace barriers is essential for designing effective interventions. This study aims to develop and evaluate a web-based workplace intervention with active breaks to reduce spinal pain among office workers.

**Methods:**

This study follows a sequential exploratory mixed-methods design. The qualitative phase will use semi-structured interviews with office workers to explore their experiences with spinal pain, active breaks, and perceived barriers to implementation. These findings will inform the development of a six-week web-based therapeutic exercise intervention, which will be evaluated through a two-arm cluster randomised controlled trial. The trial will compare an intervention group performing structured active breaks during work hours with a control group maintaining their usual routine. Primary outcomes include pain intensity (Visual Analogue Scale), spinal dysfunction (Spine Functional Index), and adherence to the program. Secondary outcomes include quality of life (EQ-5D-5L) and exercise motivation (Behavioural Regulation in Exercise Questionnaire-2). Statistical analyses will compare within- and between-group differences to assess the intervention’s effectiveness.

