### Quantitative phase

#### Design.

A two-arm cluster randomised controlled trial will be conducted following the recommendations of the CONSORT checklist [46]. A six-week online intervention will be carried out using exercise videos, taking into account the current scientific evidence and the results of the previous phase. The intervention will align with established guidelines [47], which emphasises therapeutic exercise, including strengthening exercises, mobility and stretching routines, and general physical activity, to improve musculoskeletal function and address musculoskeletal disorders.

In this study aimed at reducing musculoskeletal spinal pain among university office workers, two distinct interventions are being employed: the Intervention Group and the Control Group.

The Intervention Group will implement a six-week therapeutic exercise intervention in their workplace environment, following the program content developed in the previous phase.

Conversely, participants in the Control Group will be placed on a waiting list, advised to maintain their regular daily activities, and working hours. Upon completion of the questionnaires after the six weeks, they will gain access to the platform, receiving identical content to that of the Intervention Group.

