#### Primary outcome.

Pain intensity: Spinal pain will be assessed using the Visual Analogue Scale (VAS) [51,52], a subjective scale ranging from 0 to 10, with 0 representing “no pain” and 10 representing “the worst possible pain.” A clinically important difference (MCID) for the VAS is defined as a 30% reduction from baseline [53], which is considered a meaningful improvement in pain intensity for musculoskeletal conditions. Therefore, any reduction of 30% or greater in VAS scores will be considered a clinically significant improvement.

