#### Secondary outcomes.

Spinal pain dysfunction: Spinal pain dysfunction will be assessed using the Spanish version of the Spine Functional Index (SFI) [54,55], a self-administered questionnaire that evaluates the impact of spinal conditions on daily activities and functional abilities. In the absence of an established MCID, we will apply the distribution-based approach, calculating the MCID as 0.5 times the standard deviation of baseline scores. This method is widely used in clinical research to estimate clinically meaningful changes based on the variability within the sample when anchor-based MCIDs are unavailable [56].

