#### Adherence to the program.

Therapeutic adherence will be assessed using a self-administered diary available on the Sakai platform, where participants will record the active breaks they performed at the end of each workday. To promote adherence, reminder emails will be sent at the start and end of each week to prompt participants to complete their diary entries. Adherence data will be reviewed weekly by the research team to monitor participant engagement. If adherence remains unreported at the end of the week, a personalised follow-up email from the supervising physiotherapist will be sent at the start of the following week.

This diary serves as a tool to monitor and evaluate participants’ compliance with the intervention, providing valuable insights into their engagement with the prescribed active break regimen. The 80% adherence rate is considered satisfactory in pain management interventions [62,63].

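### The abstract names three primary outcomes and the body names one; the abstract should be aligned to VAS pain before outcome data are seen

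*Protocol article*

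**What the plan says.** Abstract, Methods: "Primary outcomes include pain intensity (Visual Analogue Scale), spinal dysfunction (Spine Functional Index), and adherence to the program". The next sentence confines the secondary list to two instruments: "Secondary outcomes include quality of life (EQ-5D-5L) and exercise motivation (Behavioural Regulation in Exercise Questionnaire-2").

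Body, Quantitative phase:

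- The heading Primary outcome is singular and covers one measure: "Pain intensity: Spinal pain will be assessed using the Visual Analogue Scale (VAS").
- The heading Secondary outcomes opens with the SFI: "Spinal pain dysfunction: Spinal pain dysfunction will be assessed using the Spanish version of the Spine Functional Index (SFI"). Quality of life and exercise motivation follow.
- Adherence has its own heading after these and is nowhere called primary: "Therapeutic adherence will be assessed using a self-administered diary available on the Sakai platform, where participants will record the active breaks they performed".
- Sample size calculation uses a pain-intensity difference of 1.5 and SD of 1.5, with alpha 0.05, 95% power and 20% dropout, and arrives at 33 per group. It mentions no other outcome.
- Statistical analysis sets one threshold, p < 0.05, and lists adherence among the variables the models adjust for.

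On the control arm, Design says: "participants in the Control Group will be placed on a waiting list, advised to maintain their regular daily activities, and working hours". It continues: "Upon completion of the questionnaires after the six weeks, they will gain access to the platform".

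**The concern.** The SFI is primary in one part of the article and secondary in another, and adherence is primary in the abstract only. Condensing does not explain this. An abstract may leave detail out, but this one adds two primary outcomes that the body does not support.

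The primary outcome is fixed in advance so that the basis for the trial's conclusion cannot be chosen after the results are known. Here one result would be read in two ways. If VAS pain shows no difference and the SFI does, the abstract would allow a report of success on a primary outcome, and the body would not.

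Adherence raises a second difficulty. The abstract names it as primary and then says the analyses will compare within and between groups to judge effectiveness. Only one arm has a programme and a diary during the comparison period.

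**Working it through.** **1. Which version does the sample size support?** Inputs from Sample size calculation: difference 1.5, SD 1.5, alpha 0.05 (taken as two-sided), power 95%, dropout 20%.

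- n per arm = 2 × (1.960 + 1.645)² × (1.5/1.5)² = 25.99, rounded up to 26.
- With dropout: 26 / 0.8 = 32.5, rounded up to 33. This is the stated figure.
- A one-sided test gives 22, and 22 / 0.8 = 27.5, rounded up to 28, which does not match. An exact t-based calculation gives 27, and 27 / 0.8 = 33.75, rounded up to 34, so the plan's figure is the usual normal approximation.

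The 33 follows from pain intensity alone, with the whole alpha of 0.05 spent on it. That agrees with the body's single primary outcome.

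**2. The two lists side by side.**

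| Outcome | Abstract | Body |
|---|---|---|
| VAS pain | primary | primary |
| SFI | primary | secondary |
| Adherence | primary | described after the secondary outcomes; model covariate |
| EQ-5D-5L, BREQ-2 | secondary | follow the SFI under Secondary outcomes |

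**3. What the abstract's version could cost.** Only VAS and SFI can be compared between arms (step 4), and the article does not say how they would combine. Each test is assumed to hold its own 5% level.

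- *Either one suffices, each at 0.05.* If independent, the family-wise error is 1 − 0.95² = 0.0975. For correlated normal test statistics, simulation gives about 0.095 at a correlation of 0.3, 0.091 at 0.5 and 0.084 at 0.7. These correlations are assumptions, as the article gives none.
- *Either one suffices, with Bonferroni at 0.025.* n = 2 × (2.241 + 1.645)² = 30.2, rounded up to 31; 31 / 0.8 = 38.75, rounded up to 39 per group. Kept at 26 evaluable per arm, power for pain falls from 0.950 to Φ(√13 − 2.241) = 0.914.
- *Both required.* Alpha is not inflated. Joint power is 0.950² = 0.90 at 26 evaluable per arm, if the two are independent and the SFI also has a standardised effect of 1.0 (both assumed).
- *VAS alone, as in the body.* Error 5%, 33 per group, no adjustment across primary outcomes.

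**4. Can adherence be compared between arms?** It is a diary of active breaks kept on Sakai. Controls are on a waiting list and reach the platform only after their six-week questionnaires. No control value exists for the comparison period, so adherence can be described in the intervention arm but not tested between arms.

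**The case against.** The strongest reply is that the operative text already points one way. The heading is singular, the SFI sits under Secondary outcomes, the sample size uses pain alone, and the study's aim is to reduce spinal pain. The outlier is a single abstract sentence. This stands: a reader might infer that the success criterion is undefined altogether, and the body does not bear that out.

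A reader might also infer that a missing multiplicity rule is itself the fault. It is not. Such a rule may sit in an analysis plan that is not shown, and with one primary outcome none is needed across primaries. The point rests on the contradiction, which an analysis plan held elsewhere would not remove from this text.

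The 9.75% is open to a fair challenge as well. It requires that the abstract governs, that either outcome alone is enough, and that the two are independent. The article states none of these, and pain and function in the same people are unlikely to be independent. The figure is therefore an upper value under a stated condition. Multiplying up to three tests (1 − 0.95³ = 14.3%) would be wrong in substance, because adherence has no between-arm test.

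Finally, the abstract does not expressly call adherence a between-group endpoint, and describing compliance in one arm against the article's 80% benchmark is legitimate. That also stands. It supports treating adherence as a process measure, and does not support listing it beside pain as a primary outcome.

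**Conclusion.** The abstract and the body disagree on which outcomes are primary, and the disagreement bears on how the trial's result would be reported. The body and the pain-only sample size favour VAS pain, so the repair is clear.

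The size depends on how the abstract would be read. If success on either VAS or SFI at p < 0.05 were accepted, the family-wise error would be up to 9.75% instead of 5%, and about 8.4% at an assumed correlation of 0.7. If both were required, there would be no inflation. Adherence cannot support a between-arm comparison under the waiting-list design.

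Three further inferences are not supported here. Any effect of campus clustering on error rates is a separate question. The second sample-size statement in Statistical analysis (moderate effect, ICC 0.05, 80% power) is also separate: it names no outcome and does not settle which is primary. Whether the registry entry matches the abstract or the body cannot be judged, since the article gives only its number.

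**What to change.** Before outcome data are seen, rewrite the outcome sentences of the abstract to match the body:

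- VAS pain intensity at six weeks is the sole primary outcome, and success is judged on it alone.
- SFI, EQ-5D-5L and BREQ-2 are secondary outcomes.
- Adherence is a descriptive process measure in the intervention arm.

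For consistency, label adherence the same way under its own heading in the body. The cost is a sentence or two of text. The 33 per group is unaffected by this change, and no alpha adjustment across primary outcomes is then needed. If the investigators do intend more than one comparative primary outcome, they should say so in both places and state whether either or both must succeed. An either-or rule with Bonferroni control would need 39 per group on the plan's own pain assumptions.

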**Discussion:**

Web-based interventions can enhance adherence to active breaks and provide an accessible, cost-effective solution for spinal pain management in sedentary workplaces. By adopting a mixed-methods approach, this study will generate valuable insights into implementing workplace exercise interventions, taking into account workers’ expectations, workplace context, and adherence factors. Findings may inform future interventions aimed at managing musculoskeletal disorders in office workers.

**Trial registration:**

ClinicalTrials.gov NCT05571124

## Introduction

### Background

Musculoskeletal disorders are a leading cause of disability worldwide, significantly contributing to work-related disability, absenteeism, and presenteeism [1]. In Europe, musculoskeletal conditions in the workforce account for up to 2% of the Gross Domestic Product, [2] with spinal pain being the most common work-related health problem, affecting 43% of the working population [3]. Notably, up to 90% of the cases are classified as non-specific, meaning they cannot be linked to a particular pathology [4,5].

Workers who spend most of their time in front of the computer are predisposed to musculoskeletal pain due to the sedentary nature of their jobs, which involve repetitive movements, prolonged postures, and low physical activity [6]. In developed countries, more than 60% of office workers report physical problems related to musculoskeletal pain, which varies depending on their job type and screen time [7].

Several risk factors for musculoskeletal disorders have been described, such as job stress, the work environment, and job-related factors [8,9]. Biopsychosocial aspects play an essential role in physical health and the suffering of spinal pain, which includes both back and neck pain, among office workers [10,11]. Given the sedentary nature of office work, both regions are commonly affected, and addressing spinal pain comprehensively ensures that the intervention is relevant to a wider range of musculoskeletal conditions. Furthermore, factors like job dissatisfaction and inadequate social support can significantly impact the quality of life for workers dealing with chronic pain [12].

Implementing ergonomic, educational and organisational strategies can benefit the office worker in reducing musculoskeletal problems [13]. While ergonomic interventions are cost-effective and feasible, a comprehensive approach that combines multiple interventions, such as workplace exercise or physical activity programs, may be necessary to achieve meaningful reductions in musculoskeletal pain [14], a comprehensive approach that includes multiple interventions may be necessary to effectively reduce musculoskeletal problems in office workers such as workplace exercise or physical activity interventions [15,16].

Therapeutic exercise in the workplace has reported improvements in pain reduction, although there is significant heterogeneity in its implementation [17]. A lack of understanding about pain and kinesiophobia, often leads workers to remain sedentary for extended periods [18]. Also, in the CUPID study [19], it was observed that workers’ expectations and low mood can influence the disability caused by musculoskeletal pain.

To develop more effective strategies, exercise interventions should not only focus on pain reduction but also address the psychosocial factors associated with musculoskeletal disorders. These interventions can enhance workers’ self-confidence in managing their condition and promoting a proactive approach to treatment [20].

Different randomised controlled trials [21,22] demonstrated that using online tools for patients with chronic pain is an effective and low-cost alternative to conventional physiotherapy treatment in pain management and reduction. These studies used multimodal approaches, incorporating both exercise and education as core components.

Although more studies are needed to know which are the best health interventions for the workplace [23], taking into account patients’ preferences for interventions and self-management skills may be a good option to maintain high levels of treatment adherence and reduce presenteeism. Maintaining high adherence to treatment is essential for successful treatment to reduce musculoskeletal disorders [24,25].

Involving participants in the design and implementation of interventions may enhance adherence by allowing modifications to lifestyle and behaviour-related risk factors [26]. Furthermore, understanding workers’ expectations, preferences and context concerning pain and exercise would enhance motivation and adherence to treatment [27].

To further support these motivational processes, this study is informed by Self-Determination Theory (SDT) [28], which identifies three essential psychological needs: autonomy, competence, and relatedness as key drivers of sustained behavioural engagement [29]. Exploring these needs of the participants can help design more effective and personalised workplace interventions.

### Objectives

This mixed-methods study aims to develop and evaluate a web-based workplace exercise intervention designed to reduce chronic non-specific spinal pain among office workers. The study first seeks to understand the perspectives of office workers on spinal pain and active breaks, and based on these findings, the effectiveness of the intervention will be assessed in improving pain management and addressing both the physical and psychosocial aspects of musculoskeletal disorders.

## Materials and methods

This study intends to utilise a sequential exploratory mixed-methods research design [30]. Initially, the investigators will conduct a qualitative phase to explore office workers’ perceptions of spinal pain and active breaks. The findings from this phase will then inform the development of the intervention, which will be tested in a subsequent quantitative randomised controlled trial.

The study will follow a three-step method:

- Qualitative Phase: Gathering and analysing qualitative data.- Connection Phase: Drawing from the qualitative insights, the structure and content of the web-based user-centred program.- Quantitative Phase: The web-based program will undergo evaluation with a sample of participants followed by the collection and analysis of quantitative data.

The sequential exploratory approach ensures that the intervention is tailored to the specific needs and contexts of office workers, enhancing feasibility and adherence. This methodological framework has been widely used in public health research to integrate qualitative insights with robust quantitative evaluation [30].

### Qualitative phase

#### Design.

A qualitative study using semi-interviews will be conducted with office workers with chronic non-specific spinal pain. This phase follows a constructivist paradigm and employs a hermeneutic-interpretative phenomenological study approach to explore participants’ lived experiences. This method provides an in-depth understanding of the experiences and meanings that guide participants’ behaviour. This methodology makes it possible to capture principles, ideas and meanings from personal stories, which can be contrasted and compared with those of other participants, exposing coincidences that make it possible to create general concepts about the problem under study [31].

The qualitative phase is essential for identifying psychosocial and contextual factors influencing spinal pain among office workers, ensuring the intervention aligns with workplace realities and behavioural tendencies. Chronic pain is shaped by an interplay of biological, psychological, and social factors, affecting pain perception, adherence, and disability [32].

Following the biopsychosocial model, this phase will explore:

Beliefs about spinal pain and its management (e.g., inevitability vs. modifiability).Workplace barriers and facilitators to active breaks (e.g., time constraints, ergonomics).Behavioural factors affecting adherence (e.g., motivation, movement-related fear).Expectations for the intervention and its feasibility in daily routines.

The interview guide also draws on SDT, focusing on how autonomy, competence, and relatedness influence participants’ motivation to engage in workplace exercise [29].

These insights will ensure the intervention targets pain reduction and addresses psychosocial barriers. The study will follow the SRQR checklist for rigorous qualitative reporting [33].

#### Sampling, sample size and method of approach.

The sample will be accessible from the different faculties of the University of Lleida, which will be contacted through the different managers on each campus. One manager from each campus will be contacted to facilitate communication with the research team. The principal investigator will oversee communicating with the different contacts at each centre. Semi-structured interviews will be conducted during working hours, either in the participants’ office or in an available room within the same faculty. Interviews will be conducted in a confidential setting without the presence of other university staff members.

The inclusion criteria consist of office workers from various campuses of the University of Lleida who have been experiencing spinal pain for more than three months, spend at least 80% of their working hours in a seated position, and lead a sedentary lifestyle that does not meet the physical activity guidelines proposed by the World Health Organisation (WHO). These criteria will be assessed using a recruitment form, including questions from the International Physical Activity Questionnaire (iPAQ) [34], which evaluates weekly levels of physical activity and daily step counts. Participants must engage fewer than 75 minutes of vigorous or 150 minutes of moderate activity per week and take fewer than 10,000 steps per day [35].

Exclusion criteria include individuals with rheumatologic conditions (e.g., rheumatoid arthritis, ankylosing spondylitis), central sensitization syndromes (e.g., fibromyalgia), or other chronic pain disorders requiring ongoing pharmacological treatment (e.g., opioids, muscle relaxants). Participants currently undergoing physical therapy for musculoskeletal conditions, those absent from work, or individuals unable to perform the prescribed exercises due to medical conditions safely will also be excluded. While this study addresses both low back and neck pain under the broader category of spinal pain, this decision reflects the high prevalence of pain in both regions among office workers, as prolonged sitting and poor ergonomics affect the entire spine rather than isolated segments.

The study sample will be selected using non-probabilistic convenience sampling. The final sample size will depend on data saturation, following the approach recommended by Vasileiou et al [36], in their study.

